# Case management and care expertise as a prevention approach for adults with intellectual disabilities (FaPP-MgB): study protocol for a randomized-controlled trial

**DOI:** 10.1186/s13063-023-07155-w

**Published:** 2023-02-23

**Keywords:** Advanced nursing practice, Nursing, Case management, Prevention, Health promotion, Intellectual disabilities, Randomized-controlled trial, Germany

## Abstract

**Background:**

Adults with intellectual disabilities have a higher prevalence of unhealthy eating habits, stress, low levels of mobility, and comparable drug consumption as the general population. Consequently, they suffer from several chronic diseases earlier and more often, but there are fewer prevention and health promotion services including this population. The goal of this study is to determine if an advanced practice nursing approach in the community with home visits is an effective way to improve the health status of adults with intellectual disabilities.

**Methods:**

We will conduct a randomized-controlled trial with waiting list design in Hamburg, Germany. Inclusion criteria are diagnosis ICD F70-F79 and exclusion criteria are care level > 3 according to the German Social Code XI or being at the end-of-life. Participants will be block randomized. The intervention consists of advanced practice nurses performing case management, social space analysis, prevention planning, and counseling through four outreach home visits on nutrition, mobility, addiction, and stress. Comparison is usual care. The primary outcome is health status (WHODAS) after 12 months. Secondary outcomes are health-related quality of life (EQ-5D) and resilience (RS-11) after 6 and 12 months. The calculated sample size is 256 with an estimated dropout of 30%. Raters and analysts will be blinded. Analysis will be performed using ANCOVAs.

**Discussion:**

By providing case management and utilizing their nursing expertise, advanced practice nurses will provide valuable input and guidance on prevention and health promotion for people with intellectual disabilities. They will close the gap between health and social care, which is prominent in Germany, through cooperation between the existing care sectors.

The findings will be disseminated in peer-reviewed journals and presented at national and international conferences.

**Trial registration:**

German Clinical Trials Register, DRKS00028771, registered 4 July 2022, Universal Trial Number: U1111-1277–0595.

## Introduction

People with intellectual disabilities^1^ account for approximately 1% of the population depending on method of measurement and context [1, 2]. They have higher risk of certain (chronic) diseases depending on context, e.g. asthma, diabetes, epilepsy, obesity, and osteoporosis as compared to the general population [3, 4, 5]. They seem to show high levels of sedentary behavior [6] and low levels of physical activity [7]. Additionally, people with intellectual disabilities are more susceptible to unhealthy eating habits [8] as well as stress [9] throughout their life and show similar levels of tobacco and alcohol consumption as the general population [10]. However, they seem to be more vulnerable to the side effects of drug consumption [11]. Therefore, they have an elevated mortality which could have been mitigated by healthcare interventions [12, 13, 14, 15].

As any other group, people with intellectual disabilities could make use of more health services with regard to prevention and health promotion. However, there are several factors that, among others, result in lower rates of received prevention and health promotion interventions [16]. First, programs enrolling people with intellectual disabilities are rare (in Germany) since professionals often do not have the competence to deal with these clients. Second, people with intellectual disabilities may have different communication patterns [17]. Third, due to a lack of data, we assume that a considerable amount of people has a lower health literacy like the general population [18, 19], and therefore, identifying suitable information regarding the topic of prevention and health promotion is difficult [20]. Fourth, the presented information (written or verbal) is often not understandable [20]. Fifth, people with intellectual disabilities might also have lower resilience [21] while facing more adversity throughout their life than the general population [22].

To address these issues, specialized care and support systems need to be established, which focus on the (social) environment as well as individual aspects [23, 24]. This implicates that some form of case management could be helpful improving the situation for people with intellectual disabilities. However, the German nursing context differs from most other countries in terms of graduation and roles.

The education of the majority of nurses takes place at vocational (nursing) schools. The opportunity to study for a primary qualification in nursing only exists for about 18 years with a considerable increase around 2010 due to an initiative for model study programs [25]. The academic qualification in nursing management, science, and education exists since the early 1990s [26]. Overall, about 2–3.2% of nurses have an academic qualification, most of them on a bachelor’s level [27]. Additionally, the German healthcare system is very physician-centered, especially with regard to prescriptions of medication and medical aids or referral to other healthcare practitioners. Consequently, Germany lags significantly behind the international developments of nursing care of other countries. Therefore, advanced nursing practice (ANP) is only seldomly implemented in Germany. There are several hospitals using advanced practice nurses (APN) expertise, but no systematic approach exists in Germany [28]. In the community setting, it is even more rare. Pilot projects in Germany most recently successfully implemented school nurses [29].

In Germany, the profession of nursing does not have a longstanding tradition in caring for people with intellectual disabilities. This field has mostly been worked by practitioners from curative education, social work, or social pedagogy. Only in recent years, in the course of the reform of the German Teilhabegesetz (Participation Act), it has been advocated to bring more health professionals into this field, as the health problems of this population group have not been given sufficient attention. We believe that APNs will be able to combine the elements of case management, prevention, health promotion, and working on the (social) environment to improve the care and health of people with intellectual disabilities as indicated by a recent systematic review on the role and key activities of APNs [30]. The project “Case management and care expertise as a prevention approach for adults with intellectual disabilities” takes up this demand and develops a prevention offer for people with intellectual disabilities from the APN understanding.

Regarding the effectiveness of case management, up to this date, there still remains only limited evidence [31, 32, 33, 34, 35, 36]. The effects of case management are not that easily measured with quantitative studies alone, because it is a complex intervention often working between the different sectors of care. Especially the impact on health outcomes might often be mitigated by other factors [37]. Nonetheless, it might help to reduce hospital admissions [31, 33, 34, 35], although there also exists contrasting evidence [36, 38]. Moreover, it can also possibly have an impact on self-care and self-management as well as the communication between healthcare professionals and the patients and the caregivers [31]. This strongly varies between populations and contexts. On the other hand, qualitative studies highlight, among other things, the improvement of access to healthcare as a door opener through coordination as well as advocacy, improved understanding of health, continuous care due to individualized care plans, networking, and emotional support [39, 40]. Considerable barriers for case management are time constraints, lack of willingness to work interdisciplinary by other health professionals, lack of training, and confusion regarding the case manager’s role [40, 41].

With respect to people with intellectual disabilities, only very few studies have been conducted on case management itself as an intervention so far [42, 43]. However, case management is usually a part of nursing itself and is included in interventions regarding prevention and health promotion for this population. The existing evidence on the effects of prevention and health promotion on adults with intellectual disabilities is sparse, although there are 17 reviews on the topic. Most of them include only a few studies. The biggest body of evidence exists for weight management and lifestyle changes with 61 studies overall [5].

Studies focusing specifically on the population at hand identified the effectiveness of physical activity interventions on maintaining and improving physical activity. Additionally, specific exercises might improve the people’s gait. However, the effect of interventions of activity and weight management alone on for example the BMI or food intake are mixed [5, 44]. The combination of interventions focusing on activity and nutrition seem to be more promising [5]. The impact of specific interventions to reduce substance use in any form or improve stress levels do not show conclusive results [5, 11, 45].

Our study will provide further insight into nurse-led case management regarding people with intellectual disabilities and ANP in Germany.

## Methods

### Objectives

The goal of the study is to (a) test the effectiveness of the ANP intervention on the health status, resilience, and quality of life of people with intellectual disabilities, (b) evaluate the process of the intervention, and (c) perform a health economic evaluation. Here, we will report on (a) and (b) only.

### Design

The study design is a randomized-controlled trial (RCT) with waiting list and superiority framework. People being in the control group (CG) will receive the intervention after completion of data collection after 12 months. It will be conducted from January 2022 to December 2024. The study is accompanied by a mixed-methods process evaluation consisting of quantitative structured interviews as well as qualitative interviews focusing on the process as well as experiences of different stakeholders (APNs, clients, caregivers, care providers in the community) as well as an inclusive research group. In the latter, people with intellectual disabilities will act as co-researchers and conceptualize their own part in the evaluation. We will report on the RCT only, because the conceptualization is finalized. The flow of participants and data collection is shown in Table 1.

**Table 1 Tab1:**
[figure not shown]
SPIRIT - Phases of trial and data collection

*IG* Intervention Group, *CG* Control Group, *HQOL* Health-related quality of life

### Participants and randomization

The study will be conducted in all seven districts of Hamburg, Germany. Therefore, participants can live in the community setting as well as in more residential care settings. A list of our cooperation partners can be found in the trial register. Inclusion criteria are a diagnosis of ICD-11 F70-F79 and being ≥ 18 years. Exclusion criteria are having a care level > 3 according to the German Social Code XI (which corresponds to severe impairments of independence or abilities), as well as being at the end-of-life.

Recruitment started in July 2022. Study participants are recruited through (a) local information events with a presentation and room for questions in various contexts, e.g., in residential institutions caring for people with intellectual disabilities, residential living groups, housing associations, cultural street festivals, and (b) mailings by the German health insurance funds AOK Rheinland/Hamburg and Mobilkrankenkasse which includes advertisements and a statement of support for the study as well as contact details of the coordinator for the APNs at the Evangelische Stiftung Alsterdorf (ESA).

Randomization is going to be conducted with the R-Package randomizeR [46] with randomly permuted blocks in size of two, four, or six [47]. The person randomizing the participants at the Bielefeld University of Applied Sciences (BUAS) is also responsible for scheduling the raters for data collection. She is going to send the list of randomized pseudonyms to the person doing the appointment coordination for the APNs at ESA. Afterwards, BUAS will inform the participants and if applicable their legal guardians in the CG and intervention group (IG) about the result of the randomization and will make appointments for data collection, while the ESA is doing calls for scheduling the APN visits. The person at BUAS is the only person that has access to the randomization procedure and keeps the list of randomizations password protected.

Group assignment will be blinded for raters as well as the analyst. Participants as well as the APNs cannot be blinded due to the nature of the intervention. The clients as well as their caregivers are instructed not to talk about the intervention before each data collection; however, it can be expected that some clients may tell the raters about the APNs visits.

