The second visit also takes place within the first month of participation and consists of a detailed assessment of health problems based on the InterRAI intellectual disability assessment [52]. A network map will be drawn to illustrate the social network of the participants. Further differentiated assessments will be used on a case-by-case level. In the aftermath, nursing problems and goals will be structured according to the ABEDL-model [53], and a case description will be prepared.

The third visit takes place in the second month and aims for the development of a prevention plan. In the prevention plan individual goals, (possible) health problems, preventive interventions, and actions to improve health as well as suitable outcomes to measure for evaluation will be formulated on the basis of the aforementioned assessments. The plan will be developed in a joint work between the client, the primary caregivers, and the APN. The fourth visit will happen after 1 year and is supposed to serve for the evaluation of the actions from the prevention plan. Moreover, overarching goals for the client's health beyond the project should be defined together with the clients and their caregivers.

Between the home visits the APNs hold liaison with the clients via their preferred ways, e.g., telephone, e-mail, or video conference. Every 2 months, the prevention plan is going to be reviewed and updated if necessary. Since it is common that people with intellectual disabilities have problems with enrolling in healthcare programs, the APNs will exercise brokering and advocacy to support them in getting the care they need. They will also gatekeep on certain interventions, if those interventions are not primarily needed. The APNs will perform single person interventions in form of counseling regarding the four areas of prevention by themselves, e.g., counseling on stress reduction if there are no suitable interventions available but will of course focus on brokering to keep it manageable. After 6 months, an individual video will be sent to the client, which focuses on motivation and resilience to keep the clients on track of their prevention plan or prompt contacts, if something is not going according to plan.

The APNs document their work in a standardized documentation system.

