### Data processing and analysis

Data will be transferred from the questionnaires to a prespecified data matrix in IBM SPSS Version 27 by two raters simultaneously based on a codebook of variables and their values. Data will be checked periodically by the project lead on double entries, wrong values, and missing questionnaires throughout the process to ensure data quality.

All outcomes can be analyzed with methods for continuous outcomes. We will perform an ANCOVA with the respective outcome at the respective time point (*t*_1_, *t*_2_) as the dependent variable and the baseline value (*t*_0_) as the covariate. We are going to test three hypotheses with a Bonferroni adjusted alpha of 0.025 each:

The IG differs from the CG regarding:The health statusThe health-related quality of lifeResilience

We will use intention-to-treat analysis for people dropping out of the study, if we have any data on them as well as participants discontinuing the intervention.

The process evaluation will be analyzed with descriptive statistics, reporting absolute and relative frequencies as well as measures of central tendency and dispersion suitable for the respective data level of the items.

Sample size calculation has been performed with the software G*power 3.1 [57]. Based on an effect size of *f* = 0.23 for an ANCOVA, a significance level of 0.05 with Bonferroni correction to 0.025, and a power of 0.8, 184 participants have to be recruited. As a conservative decision, we estimated a 30% dropout rate due to the complexity of the intervention and the 1-year time frame as well as the specifics of the target population. Therefore, we plan to include 256 people with intellectual disabilities (128 per group) in this study.

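### As written, participants learn their allocation before or when data-collection appointments are made, so the baseline covariate may be measured after disclosure and possibly after the first APN visit

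*Protocol article*

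**What the plan says.** The section Participants and randomization gives the steps in order. One person at the evaluating university (BUAS) randomises. Then: "She is going to send the list of randomized pseudonyms to the person doing the appointment coordination for the APNs at ESA". The step after that is disclosure: BUAS tells participants, and guardians where there are any, "about the result of the randomization and will make appointments for data collection, while the ESA is doing calls for scheduling the APN visits".

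Other parts of the article bear on this:

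- **Blinding.** Raters and the analyst are blinded; clients and nurses are not. The safeguard offered is an instruction: "The clients as well as their caregivers are instructed not to talk about the intervention before each data collection". The article concedes that this may fail, since "it can be expected that some clients may tell the raters about the APNs visits".
- **Intervention.** The first home visit builds the relationship with client and caregiver and screens for health problems. "The second visit also takes place within the first month of participation".
- **Outcomes and data collection.** The outcome evaluation runs from t0 to t2. The text gives t0 no position relative to randomisation, disclosure or the first visit. WHODAS is proxy-rated, EQ5D-VAS is both proxy- and self-rated, and RS-11 is self-rated.
- **Data processing and analysis.** Each outcome is analysed by ANCOVA with its own t0 value as the covariate. No other covariate is named. "We will use intention-to-treat analysis for people dropping out of the study, if we have any data on them", and the same applies to those who discontinue the intervention.
- **Roles and responsibilities.** The foundation that delivers the intervention (ESA) recruits, and BUAS collects the data. The disclosure contact is therefore the first contact between BUAS and participants that the article describes.

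**The concern.** ANCOVA on a baseline value is safe in a randomised trial because the baseline cannot have been influenced by the allocation. That holds when the baseline is taken before anyone who supplies it knows the group. The order written here does not secure it. If t0 is one of the appointments made at or after disclosure, a client or guardian answers it knowing whether nurse visits start now or in a year. If a visit has already taken place, the nurse and the caregiver may also have discussed the client's health problems.

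Rater blinding does not remove this risk, because the information comes from the respondent. The model would then adjust for something the allocation may have changed, and part of any difference at t0 would be carried into the estimated effect at 12 months.

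**Working it through.** **1. The order of events.** The stated sequence is: randomise; send the list to ESA; inform participants and guardians and make data-collection appointments; meanwhile ESA calls to schedule APN visits. The data-collection appointments are not limited to the 6- and 12-month interviews. The instruction not to talk about the intervention applies to each data collection, and the rater's guess of the allocation is part of the outcome questionnaire with no stated exception for t0. So the text allows t0 after disclosure. Because two visits fall in the first month and are scheduled in parallel, it also allows t0 after an APN visit, but it does not say that this happens.

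**2. The plan's own figure.** Inputs from Data processing and analysis: f = 0.23, alpha 0.025, power 0.80, N = 184. For a two-group ANCOVA with one covariate, the noncentrality is N × f² = 184 × 0.0529 = 9.73, with 1 and 184 − 3 = 181 degrees of freedom. Power is 0.804, so 184 reproduces. For two equal groups d = 2f = 0.46 residual SD.

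**3. Planned effect in raw SD.** With r the correlation between baseline and 12 months (assumed, and equal to the slope if the SD is the same at both times), the planned effect is 0.46 × √(1 − r²).

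**4. Bias.** The ANCOVA estimate is the difference in 12-month means minus slope × difference in baseline means. If knowledge of allocation moves t0 in one arm by s SD and leaves t2 untouched, the estimate moves by r × s. The values of r and s below are assumptions.

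| r | Planned effect (raw SD) | Bias, s = 0.1 | % of planned | Bias, s = 0.2 | % of planned |
|---|---|---|---|---|---|
| 0.5 | 0.398 | 0.05 | 13 | 0.10 | 25 |
| 0.6 | 0.368 | 0.06 | 16 | 0.12 | 33 |
| 0.7 | 0.329 | 0.07 | 21 | 0.14 | 43 |

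**5. What that does to the test at N = 184.** If the shift is towards better health at t0 in the intervention group, it works against a true benefit. Power falls from 0.80 to 0.68 (r = 0.5, s = 0.1) or to 0.32 (r = 0.7, s = 0.2). With no true effect, the rejection rate rises from 0.025 to 0.036 and 0.18 in the same two cases.

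**6. Direction.** Respondents stay unblinded at t2. If the same reporting tendency moves t2 by s₂, the net change is s₂ − r × s. With s₂ = s = 0.2 and r = 0.6 this is 0.20 − 0.12 = 0.08 SD, opposite in sign to the case where only t0 moves. The sign therefore cannot be settled from the document.

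**The case against.** The strongest reply is that the decisive evidence is not visible. The Design section says Table 1 shows the flow of participants and data collection. That table is the SPIRIT schedule, it is not reproduced in the text at hand, and it may well put t0 before allocation. The full protocol is also not shown. The quoted sentence does not name t0, its paragraph is mainly about who holds the list and who calls whom, and the article calls t0 the baseline value. This stands as a limit: one cannot say that the plan lacks a pre-allocation baseline. It does not remove the point, because the section states an order, and if Table 1 differs the two disagree.

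Several stronger readings are tempting and are not supported:

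- **That t0 follows the start of the intervention.** Parallel telephone scheduling does not fix the order of the visits, and the first month of participation has no stated starting point.
- **That every baseline respondent is unblinded.** Participants and, where applicable, guardians are told. The proxy may instead be a family member or professional caregiver, and the text does not say that these people are informed at that stage.
- **That disappointed controls refuse t0 and drop out of the analysis.** Nothing in the article says so. Controls are offered the intervention after 12 months, and retention steps are listed. The rule on having any data is worded for dropouts in general.
- **That a baseline shift passes in full into the effect.** It is multiplied by the slope, and a matching shift at t2 would offset it.

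**Conclusion.** The concern holds as a matter of the written order. Allocation is disclosed before, or in the same contact as, the making of data-collection appointments, while APN visits are being scheduled. Nothing visible protects t0 from either. The sole named covariate of the primary model, for a proxy-reported outcome, may therefore be a post-disclosure measurement. That the first APN visit may also precede it is a possibility only.

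The document does not show that any baseline was in fact taken late. The 13 to 43% range is illustrative: it rests on assumed slopes of 0.5 to 0.7, assumed shifts of 0.1 to 0.2 SD in one arm, and an unaffected t2, and the direction is unknown. The sample size is not affected. Whether people were lost between randomisation and t0, and whether that differed by arm, is an open question that a simple count would answer.

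**What to change.** **Wording.** State in Participants and randomization that t0 is completed and logged before the allocation is released to ESA or to participants and guardians, and that no APN contact takes place before t0. Reconcile this with Table 1. If Table 1 already places t0 before allocation, correcting the sentence is enough.

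**For participants already enrolled in the other order.** Recruitment was due to end in January 2023, before the article appeared, so this part matters most.

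- Record the dates of t0, disclosure and first APN contact. The questionnaire already holds the date of data collection and the APNs document their work, so the disclosure date is the main addition.
- Report by arm how many people were randomised but have no t0.
- Add a sensitivity analysis of the 12-month outcome that does not adjust for a post-disclosure t0 value: unadjusted, or adjusted only for fixed characteristics such as age and sex. Keep all randomised participants with outcome data. Simply excluding people with a post-disclosure baseline would not serve, because if all baselines followed disclosure nobody would remain.

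**Cost.** There is a short wait between t0 and allocation, and some precision is lost in the sensitivity analysis. Without the baseline covariate the standard error grows by about 1/√(1 − r²): 1.15 at r = 0.5, 1.25 at r = 0.6 and 1.40 at r = 0.7 (assumed values). The sensitivity analysis removes only the bias that enters through t0. It does not address unblinded reporting at 12 months.
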